#### Sample size and recruitment

As we have a demand study, all children enrolled for dental treatment at the dental unit will be potentially recruited for this before-and-after study and no sample size is required. The child will be our unit of analysis for that. As previously described, refusals and non-compliance with non-face-to-face consultations will also be registered as outcomes. At least five attempts to contact participants who accept to participate will be used. In these attempts, we will consider different manners of communication, including phone calls, text and Whatsapp messages, email messages (when possible).

### Randomized controlled trial (controlled by waiting list)

#### Main purpose

We outlined a randomized patient-controlled study on the waiting list for care to assess the impact of teleservice implementation under the patients' and their families' perspectives, permitting comparison with a reference, in this case, those patients who are not participating in the Teletrailer program yet.

#### Participants: eligibility criteria

Children eligible for the previous study are also eligible for this one and is moved forward to the randomization step. Similarly, those who cannot be contacted after several attempts will be excluded from the sample. Children or guardians who do not agree to participate in the research were excluded from this randomizable sample.

#### Interventions

The family (including all children enrolled at the unit from the same family) will be randomized using stratified randomization by one researcher to one of the groups (intervention vs waiting list). The stratification will be performed considering the dentist will provide the non-face-to-face consultation and the week for inclusion. In this way, balanced randomization was obtained per professional each week.

Randomization order will be generated by the website sealedenvelope.com. The list will be stored under the supervision of the person responsible for randomization ([name]) and the principal investigator ([name]), in cloud storage and on a USB stick. The dentist who will provide the dental care will be unaware of randomization. They will receive the list with families/patients they are supposed to care for each week sent via email by the person in charge of randomization.

The two groups will differ according to the time of application of the intervention and outcome assessment. The non-face-to-face intervention group will receive the intervention immediately after randomization (t0). Then, after two weeks, the outcome will be measured as described further (t2). The waiting list group (control) will not receive the intervention at this time  and then assessed after the same period to permit controlling the answers (t2). Once this is done, the children on the waiting list will receive the intervention regularly (t3) and become part of the previously detailed list of before-and-after study participants. However, for the present RCT, only data without intervention will be considered (t2). The intervention will be provided as described in the before-and-after study *Interventions* section. Both groups will have been contacted by a research team member to explain the study and will have answered a baseline questionnaire previous to randomization (t-2). At this time, all participants will know the teleservice will be available, but they will not know when that will happen.

#### Outcomes

We set the family's perception of dental care quality as the  primary outcome. We will consider the caregiver's perspective (those who participate in the non-face-to-face consultation) measured two weeks after the intervention (teleservice test group) or two weeks after waiting for care (control group) (Figs. 2, 3). The SERVQUAL questionnaire will be used [24] (Additional file 3). SERVQUAL is a summary instrument of multiple scales, with a high level of reliability and validity already used in Portuguese [24]. It can be used to understand users' expectations and perceptions concerning a wide range of services. In the present study, it is supposed the participants evaluate the degree to which they perceived the proposed service.

The questionnaire consists of 22 items, divided into 5 dimensions related to the service (tangible aspects—appearance of physical facilities, equipment, personnel and communication materials; reliability—ability to perform the promised service safely and correctly; responsiveness—willingness to help clients and provide prompt service; assurance—knowledge and courtesy of employees and their ability to inspire trust and empathy—personalized attention given to customers) [25]. A total of 100 points is allocated among the five dimensions.

As secondary outcomes, we define the gap between users' perception and expectations, each partial assessment for five different domains included in the SERVQUAL questionnaire, and finally, the overall participants' perception of the service.

A model previously proposed was used to detect the gap between users' perceptions and expectations [26]. For that, the SERVQUAL questionnaire was applied in two different moments (before and after receiving care). Then, the difference between the scores that customers attribute to the different pairs of statements. After consent to participate in the study, the baseline questionnaire will be sent to participants when contacted to participate in the study. This baseline assessment (t-2) should be done two weeks before the allocation (t0). We will calculate the mean score attributed in the baseline SERVQUAL assessment (t2) in each dimension to evaluate individual dimensions separately. Finally, one extra item was included besides the mentioned questionnaire (t2): "How do you feel about these service attributes that are already provided?". It was scored on a 5-point Likert-type scale of "very bad (1)" to "very good (5)." to identify overall participants' perceptions.

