#### Statistical methods

We will adopt the intention to treat analysis for both clinical trials, and all recruited participants will be considered when expressing our findings. Imputations of the outcomes will be considered whenever missing data is detected. In these cases, using conditional imputation methods will be used.

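### The RCT primary outcome ties its respondent and its test-arm timing to attending the teleconsultation, which by t2 only the intervention arm can have done, leaving room for one-sided selection

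*Protocol article*

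**What the plan says.** All places are in the protocol article.

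- **RCT, Outcomes.** The primary outcome is the family's perception of care quality on SERVQUAL. On who answers, the caregivers are specified as "those who participate in the non-face-to-face consultation) measured two weeks after the intervention (teleservice test group". On timing, the test arm is counted from the intervention and the control arm "or two weeks after waiting for care (control group".
- **RCT, Interventions.** The intervention arm is treated straight after randomisation (t0) and assessed at t2. For the other arm: "The waiting list group (control) will not receive the intervention at this time". Controls are assessed at t2 and treated afterwards, at t3. Before randomisation, both groups "will have answered a baseline questionnaire previous to randomization (t-2".
- **Abstract, Methods.** The primary outcomes are measured two weeks from randomisation.
- **Statistical methods.** "We will adopt the intention to treat analysis for both clinical trials, and all recruited participants will be considered when expressing our findings". Also: "Imputations of the outcomes will be considered whenever missing data is detected", followed by "In these cases, using conditional imputation methods will be used".
- **Before-and-after study, Outcomes and Sample size.** Absences, delays, non-compliance and connection problems are foreseen and recorded. No rate is given.
- **RCT, Sample size.** The planned difference is 0.17 with SD 0.53. The minimum sample is 306, raised to 368 families for losses.

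**The concern.** A respondent should be identifiable in the same way in both arms, by something fixed before allocation. Here the description uses an event that happens after randomisation and, up to t2, in one arm only. Every control family can be assessed at t2 without having attended anything. For an intervention family that never connects, the RCT section names neither who answers nor the date from which the two weeks run. For a family whose consultation is late, counting from the intervention moves the assessment later than in controls.

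If study staff followed the wording literally, SERVQUAL would not be collected from intervention non-attenders. Their scores would be missing in one arm for a reason linked to the service under test. Imputation could then draw only on attenders in that arm, and would correct the selection only so far as recorded covariates explain how the two kinds of family differ. This concerns the primary contrast, and ratings not collected at t2 cannot be recovered at the analysis stage.

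**Working it through.** **Step 1: the plan's own figure.** Inputs from the RCT sample-size section: difference 0.17, SD 0.53. Alpha, sidedness and power are not stated. I assume two-sided 5%, 80% power and 1:1 allocation.

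n per arm = 2 × (1.96 + 0.842)² × 0.53² / 0.17² ≈ 152.6, rounded up to 153, so 306 in total. This matches. 306 × 1.2 = 367.2, rounded up to 368, or 184 per arm. The point does not depend on these figures; they supply the scale.

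**Step 2: the wording applied to each kind of family.**

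| Family | Consultation before t2? | Respondent by the literal wording | Time of measurement by the literal wording |
|---|---|---|---|
| Intervention, attends at t0 | yes | attending caregiver | two weeks from randomisation |
| Intervention, attends late | yes | attending caregiver | two weeks from randomisation plus the delay |
| Intervention, never attends | no | none | none |
| Waiting list | no, due at t3 | none, if attendance is required | two weeks of waiting |

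The last row shows that the literal wording cannot be the full intention, because the same sentence measures controls. The third row shows what is left unsettled. The abstract's timing and the Outcomes timing agree only if every consultation takes place at t0.

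**Step 3: size, if non-attenders went unmeasured.** Let q be the share of intervention families that never attend, and d the gap in SD units by which attenders would rate above non-attenders. Both are assumptions. The attenders' mean exceeds the whole arm's mean by q × d × SD, so with all controls kept:

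bias = q × d × 0.53

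With no true effect, SE = 0.53 × √(1/(184(1−q)) + 1/184), and the two-sided error is Φ(bias/SE − 1.96) + Φ(−bias/SE − 1.96).

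| q | d | Bias | Share of 0.17 | Type I error |
|---|---|---|---|---|
| 10% | 0.1 | 0.0053 | 3% | 5.1% |
| 10% | 0.3 | 0.0159 | 9% | 5.9% |
| 10% | 0.5 | 0.0265 | 16% | 7.5% |
| 20% | 0.1 | 0.0106 | 6% | 5.4% |
| 20% | 0.3 | 0.0318 | 19% | 8.4% |
| 20% | 0.5 | 0.0530 | 31% | 14.8% |
| 30% | 0.1 | 0.0159 | 9% | 5.8% |
| 30% | 0.3 | 0.0477 | 28% | 12.3% |
| 30% | 0.5 | 0.0795 | 47% | 25.7% |

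Example for q = 20%, d = 0.5: bias 0.20 × 0.5 × 0.53 = 0.053; SE 0.0586; ratio 0.904; error 0.146 + 0.002 = 0.148.

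If SERVQUAL is obtained from every randomised family and analysed as allocated, this bias is zero whatever q and d are.

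**The case against.** The strongest reply is that the parenthesis only says which family member answers. Families are randomised and one representative responds, and controls will have a consultation later, so it can mean the caregiver who attends or will attend. The word 'only' is not in the text. The RCT Interventions section and the abstract already support a t2 at two weeks from randomisation, and the statistical section commits to intention to treat. A missed consultation is also not a missed questionnaire, since every family was reached at t-2.

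Most of this stands. A reader might infer that non-attenders are excluded and that the intention-to-treat comparison is therefore broken. The article does not support that, because nothing in it removes them from the RCT. The expected absences and connection problems are listed for the before-and-after study, without a rate. It is also not documented that non-attenders would rate the service lower.

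A reader might further infer that conditional imputation means single or mean-type imputation, with intervals that are too narrow. The article does not say so. Conditioning on covariates is equally a feature of multiple imputation, and such detail commonly sits in an analysis plan, which is not shown. That criticism is not made here.

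The reply does not settle two things. Even on the milder reading, the RCT section does not say who answers for an intervention family that never attends. The start of the clock in the Outcomes section still differs from that in the abstract whenever a consultation is not held at t0.

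**Conclusion.** The point holds as a badly fixed definition of who is measured, and when, for the primary outcome. The respondent is described by a post-randomisation event that only one arm can have experienced by t2, and the test-arm clock starts at that same event. This conflicts with the timing in the abstract and fits poorly with intention to treat.

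Bias is possible but not shown. Its illustrative size is about 0.005-0.08, or 3-47% of the planned 0.17. That rests on three assumptions: 10-30% of intervention families do not attend, attenders would rate 0.1-0.5 SD higher, and non-attenders go unmeasured while all controls are measured. It should be settled in the protocol, because it governs data collection and cannot be repaired afterwards.

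**What to change.** In the RCT Outcomes section:

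- Define the respondent in both arms as the caregiver who answered the t-2 questionnaire. The gap outcome compares SERVQUAL at two moments, so using the same person at both also serves that analysis.
- Set t2 at two weeks after randomisation in both arms, and collect SERVQUAL from every randomised family whether or not the consultation took place. Controls already answer without having had one, so non-attending families can do the same.

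In the statistical section, state that families are analysed as allocated and that an attenders-only comparison is supplementary.

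The cost is revised wording and a questionnaire to families who have already consented and been contacted. The estimated effect may be smaller. If 0.17 is the difference among attenders and non-attenders gain nothing, the expected difference is 0.17 × (1 − q): 0.153 at 10% non-attendance and 0.119 at 30%. With 184 per arm all measured, power would be 79% and 58%, against 87% with full attendance. That dilution belongs to the intention-to-treat effect the plan already promises.

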#### Sample size and recruitment

The sample calculation was made using the application sample-size.net and considered the primary outcome for the RCT as a reference. As more than one dimension is considered in evaluating the primary outcome, we consider an average between them. A hypothetical user's difference between the perceived and the expected users' quality appraisal related to a regular health service clinic [27] was used to estimate a minimum difference for this trial, aiming at a more conservative calculation. The minimum difference expected was set, then, as 0,17 (effect size) and a standard deviation of 0,53 assumed (based on the worst case scenario in the referred study) [27]. A minimum sample of 306 users or family representatives in the RCT was estimated. Extra 20% was added to compensate for possible losses, resulting in a final sample of 368 families recruited. Thus, the first 368 families from the unit's care list will be included (randomized). To reach the required number of children, all participants registered at the mobile dental care unit will be invited to participate in this study by telephone or social media contact or message, as detailed in the before-and-after study.

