##### The RCT (waiting list controlled)

This study will first compare the satisfaction with the health care received using the SERVQUAL score between the groups (with and without technology-mediated care). We will use an appropriate statistical test depending on the distribution of scores. The scores assigned for the perception of each dimension will also be compared. Appropriate regression analyses may also be performed to verify other variables' influence, besides the group (test vs control) on users' perception of the received care.

We will also compare the gaps (difference between expected and perceived) between groups. Comparisons between the perceived and the expected in each one of the groups will also be performed. Once again, distributions will be checked to choose the appropriate statistical approach to be used.

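### The RCT sample size takes its inputs from a perceived-versus-expected contrast, so 80% power for the unadjusted primary test depends on an unstated SD; adjusting for the baseline SERVQUAL score removes that dependence

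*Protocol article*

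**What the plan says.** All references are to the protocol article, in the section on the randomized controlled trial and its statistical methods.

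- **Primary outcome (Outcomes).** The family's "perception of dental care quality as the" primary outcome, taken from the caregiver by SERVQUAL two weeks after the teleconsultation or two weeks into waiting (t2).
- **Secondary outcome (Outcomes).** "As secondary outcomes, we define the gap between users" and their expectations is listed here, obtained from SERVQUAL applied at t-2 and again at t2.
- **Primary comparison (The RCT, waiting list controlled).** The study will "first compare the satisfaction with the health care received using the SERVQUAL score between the groups", with a test picked according to the distribution of scores. Regression on other variables is optional. Gaps are compared afterwards, as a separate item.
- **Sample size (Sample size and recruitment).** The calculation "considered the primary outcome for the RCT as a reference" and averages over the dimensions. The target comes from a "difference between the perceived and the expected users" quality appraisal in a regular clinic, reported in a cited study. Then: "The minimum difference expected was set, then, as 0,17 (effect size) and a standard deviation of 0,53 assumed", the SD being the worst case in that same study. The result is 306, raised by 20% to 368 families. Alpha and power are not printed.
- **Baseline (Interventions, and Outcomes).** Both arms answer a questionnaire before randomisation (t-2), and it is the SERVQUAL.

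**The concern.** The calculation is declared to be for one quantity, but its target difference is drawn from another. A contrast between what users expected and what they perceived is not a contrast between a teleservice arm and a waiting-list arm in perception alone. No sentence carries the 0.17 or the 0.53 across.

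The SD matters most. The article does not say what kind of score has an SD of 0.53. If it is the SD of a perception score, it is the right kind of input for the planned test. If it is the SD of a gap, the SD of perception depends on how strongly perception and expectation are correlated, and it may be smaller or larger than 0.53. The power of the planned comparison moves with it, in either direction, and the reader cannot tell where it lies.

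**Working it through.** **Inputs.** Difference 0.17, SD 0.53 and total 306 (Sample size and recruitment). Equal allocation, read from the balanced randomisation (Interventions). Assumed, because not printed: two-sided 5% and 80% power. Also assumed: the correlation r between the t-2 and t2 scores, taken as 0.2, 0.5 and 0.7.

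**1. The plan's own figure.** For two independent means, n per arm = 2 × [(1.96 + 0.8416) × 0.53 / 0.17]² = 152.6, so 153 per arm and 306 in total. This is an exact match. Then 306 × 1.2 = 367.2, so 368. Other settings do not give 306: the totals are 350 and 410 at two-sided 85% and 90% power, and 242, 280 and 334 at one-sided 80%, 85% and 90%. A paired or one-sample test of a gap at 80% power would need only [(1.96 + 0.8416) × 0.53 / 0.17]² = 76.3, so 77.

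Two things follow. The calculation has the between-arm form of the primary comparison. And 0.17 was used as a raw difference, with standardised value 0.17 / 0.53 = 0.32.

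**2. Unadjusted test when 0.53 is a gap SD.** With equal variances, gap SD = σ√[2(1 − r)], so the perception SD is σ = 0.53 / √[2(1 − r)]. This gives 0.419, 0.530 and 0.684 for r = 0.2, 0.5 and 0.7.

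**3. Unadjusted test when 0.53 is a perception SD.** σ = 0.53 whatever r is, and power is 80%.

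**4. ANCOVA on the t-2 score.** The residual SD is σ√(1 − r²).
- Gap reading: 0.411, 0.459 and 0.489.
- Perception reading: 0.519, 0.459 and 0.378.

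Power for a difference of 0.17 with 153 per arm, two-sided 5%:

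| Meaning of 0.53 | Analysis | r = 0.2 | r = 0.5 | r = 0.7 |
|---|---|---|---|---|
| Gap SD | Unadjusted | 94% | 80% | 58% |
| Gap SD | ANCOVA | 95% | 90% | 86% |
| Perception SD | Unadjusted | 80% | 80% | 80% |
| Perception SD | ANCOVA | 81% | 90% | 97% |

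**5. Why ANCOVA is safe on both readings.** The fitted slope is the one that makes the residual variance of (t2 − slope × t-2) smallest. A slope of 1 gives the gap and a slope of 0 gives raw perception. The residual variance therefore cannot exceed either one, and this does not need equal variances. If 0.53 is right for the gap or for perception, it is at least as large as the ANCOVA residual SD.

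**The case against.** The strongest reply is that the article does not power the trial on the gap. It uses a perceived-versus-expected difference openly, as a benchmark for the smallest difference of interest, and then puts it into a two-group formula that matches the primary comparison. That stands. Borrowing an external contrast to set a target is ordinary practice, and 306 is correct if perception at t2 has an SD of 0.53.

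It is also fair that 0.53 is nowhere called a gap SD, so the 94% to 58% range rests on one possible reading, on equal variances and on assumed correlations. At r = 0.5 the gap SD and the perception SD coincide. This too stands, and it is why the range is offered as sensitivity and not as an estimate.

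Two stronger readings are tempting, and the document supports neither.
- A reader might take the words in "The minimum difference expected was set, then, as 0,17 (effect size) and a standard deviation of 0,53 assumed" to mean that 0.17 is a standardised effect, so that the trial is far too small. The SD is printed in the same sentence and 306 follows exactly from the raw values. The label is loose and changes no number.
- A reader might infer from "A total of 100 points is allocated among the five dimensions" that the primary score lies on a 100-point scale, where 0.17 would mean nothing. The article describes the instrument there. It does not put the primary score on that scale, and the questionnaire itself is in an additional file that is not shown.

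What the reply does not answer is the missing step from the cited contrast to between-arm perception. Calling the SD a worst case does not supply it: a worst case for a gap need not be a worst case for perception.

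**Conclusion.** The point holds as one of unjustified inputs. The arithmetic is right and no power shortfall is shown. A reader might conclude that the RCT is underpowered, but the article does not support that: on the gap reading, unadjusted power falls on either side of 80% depending on the correlation, and on the perception reading it is 80%.

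What is established is narrower. The planned unadjusted comparison has 80% power for a raw difference of 0.17 only if the t2 perception SD is about 0.53, and the article does not show that it is. Under the gap reading, power at 153 per arm is 94%, 80% or 58% at r = 0.2, 0.5 or 0.7. An analysis using data already planned lifts this to 95%, 90% and 86%, and loses nothing under the perception reading.

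These figures assume two-sided 5%, equal arms, equal variances at t-2 and t2 for the tabulated values, and that the SD from the cited study carries over to these families. Whether 0.17 is a worthwhile between-arm difference in perception is a separate judgement that no analysis method settles.

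**What to change.** 1. In the RCT statistical methods, make the primary analysis an ANCOVA: the t2 perception score regressed on arm and on the t-2 SERVQUAL score. This replaces the unadjusted test chosen by distribution and turns one optional regression into the named primary analysis.
2. In the sample-size paragraph, say whether 0.53 is the SD of a gap or of a perception score, and note that under ANCOVA it is a conservative input on either reading. State alpha and power, and add a sentence on why 0.17 is a suitable between-arm difference in perception.
3. Call 0.17 a raw mean difference (standardised 0.32) instead of an effect size.

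The first item is the substantive change; the other two are clarifications. The cost is one covariate that is already collected from both arms before randomisation, and a few reworded sentences. No extra families are needed, and 306 and 368 can stay as they are.
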